### Recruitment of Control Subjects

Each case will be matched with four controls randomly selected from those who have undergone dental treatment at the same dental practice from which the case originated. If access cannot be obtained to records from the originating dental practice, then a similar type of practice e.g. private practice or hospital - based practice, within a 10 km radius will be approached to provide control subjects. They will be matched for age (>50 years), gender and visit window period and will have no known defect in dental wound healing. If controls cannot be matched to the 6-month visit window period then they will be matched to within 12 months of the visit window period. Controls will be contacted by mail as for cases to obtain informed consent to study participation.

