### Setting and study time frames

The study will take place in Victoria, the second most populous State in Australia with a population of approximately 5 million people. The visit window period study period will be March 1^st ^2006 until August 31^st ^2006. Participants in the study will have been treated in specialist oral and maxillofacial and special needs dentistry settings during the visit window period. Control subjects will have attended local community based referring dental practices. A flow diagram of the study protocol is depicted in Figure 2.

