#### Part 1: Demographic information

Specialist information, patient details (name, date of birth, gender, address and telephone number), name of referring practitioner, referring practitioner contact details, date of presentation of oral problem and referral to specialist date will be collected initially. A list of all dates within the visit window period together with an outline of each visit will be recorded. The demographic data will be coded for each individual and the code used in all subsequent data collection in order to de-identify information as per ethical requirements.

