The present study also relies on recruitment of specialists to allow access to patient records followed by recruitment of cases and controls. All oral and maxillofacial specialists and special needs dentists in the state of Victoria will be invited to participate in the study but it will be difficult to control for ascertainment bias. Are practitioners who see delayed dental healing and ONJ more willing to allow review of their patient records? Are those who have a greater interest in the role played by bisphosphonates more likely to want to become involved? It is difficult to control for this even with the use of random sampling because practitioners' consent is required to allow file review. To some degree the same can also be said for patients with delayed dental healing. The patient information and consent brochure stipulates that this is an important study to further our understanding of the link between delayed dental healing and bisphosphonate use. Whether an individual who has taken a bisphosphonate may be more or less likely to participate is difficult to determine. Another potential limitation of the study is recollection bias given that some data will be collected via participant telephone interview. Furthermore, control subjects reading the patient information and consent brochure may feel that the study does not really benefit them and hence may be less likely to respond. The same can also be said for the general dental practitioners via whom the control subjects will be identified. If they have little experience with patients taking bisphosphonates or delayed dental healing, then they may have little motivation to allow a third party to access their patient records.

A key feature of the present study relates to the definition of DDH and ONJ. In 2005 the definition of osteonecrosis of the jaw was unclear and constantly changing in the literature and as such it was difficult to adhere to a single definition. The main disparity at the time was related to the length of time a wound took to heal before it fell into the category of osteonecrosis of the jaw. Initial healing, that is re-epithelialisation, of dental wounds such as those from dental extractions usually takes between 1 and 2 weeks [43]. Once the clot forms, fibrin and connective tissue begins to develop before the wound (in this case a dental socket) is closed over by epithelium. It then takes some weeks for the underlying socket to fill with bone and healing to be complete.

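### The fallback for control practices asks only for a similar practice within 10 km, not a referring one, so substitute controls may lie outside the source population and may bias the odds ratio

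*Protocol article*

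**What the plan says.** The Methods section on setting and time frames gives the general rule for controls: "Control subjects will have attended local community based referring dental practices". The Abstract says the same.

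The section on recruitment of control subjects gives the working rule: "Each case will be matched with four controls randomly selected from those who have undergone dental treatment at the same dental practice", meaning the one that the case came from. It then provides for failure: "If access cannot be obtained to records from the originating dental practice, then a similar type of practice", with private and hospital-based practice as its examples of type, "within a 10 km radius will be approached to provide control subjects". On the other conditions it says: "They will be matched for age (>50 years), gender and visit window period and will have no known defect in dental wound healing".

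Cases are found only by screening the files of oral and maxillofacial surgeons and special needs dentists who agree to take part (sections on dental specialist recruitment and case recruitment). The data collection form records "name of referring practitioner, referring practitioner contact details".

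The Discussion lists willingness to give access as a limitation. Of the general dentists through whom controls are found, it says: "If they have little experience with patients taking bisphosphonates or delayed dental healing, then they may have little motivation" to open their records. It does not connect this remark to the fallback.

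**The concern.** There are two separate issues.

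**Eligibility of the substitute practice.** In a case-control study, a control should be someone who would have been counted as a case had the outcome occurred. Here that means someone whose non-healing wound would have led to a participating specialist. Taking controls from the case's own practice, or from another practice that refers to the same specialist, largely secures this. The fallback replaces the referral link with similarity of type and distance, and neither guarantees it.

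**Selection by willingness.** The fallback operates when access fails and ends with a practice that grants it. If willingness goes with bisphosphonate experience, as the Discussion suggests it may, cases from lower-use practices are compared with controls from higher-use practices. Control exposure enters the odds ratio directly, so a real association could be understated and power lost. Nobody could see this afterwards unless the substituted sets had been marked when they were recruited.

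**Working it through.** **1. The passages side by side**

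| Source of controls | Referral link required? |
|---|---|
| Abstract; setting section | Yes, referring practices |
| First choice: the case's originating practice | In effect yes, since the case reached the specialist from there |
| Fallback: similar type within 10 km | Not stated |

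This part needs no figures. The condition stated in the general rule is absent from the fallback.

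**2. The plan's own figures**

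From the power section: 30% exposure in cases, 10% in controls, 54 cases, 215 controls, 90% power. Alpha is not stated, so two-sided 5% is assumed.

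- Odds ratio = (0.30/0.70) / (0.10/0.90) = 3.86, against the protocol's 3.85.
- The two-proportion formula with continuity correction and four controls per case gives 54 cases (270 in total, against 269).
- Power at 54/215 is 90.2%.

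The planned sample size therefore reproduces and is not in question.

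**3. Effect of substitution: simple mixture**

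Let *s* be the share of matched sets with substitute controls and *q* the exposure in substitute practices. **Neither is in the protocol; both are assumptions.** The one related figure is the 19% upper limit for any bisphosphonate use in the power section, used here as the top value of *q*.

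Control exposure: p0 = 0.10(1 − s) + q·s. Odds ratio: (0.30/0.70) / (p0/(1 − p0)).

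| s | q | p0 | Odds ratio | Power (continuity-corrected) |
|---|---|---|---|---|
| 0 | – | 0.100 | 3.86 | 90% |
| 10% | 12% | 0.102 | 3.77 | 90% (89.5%) |
| 25% | 15% | 0.1125 | 3.38 | 85% |
| 50% | 15% | 0.125 | 3.00 | 79% |
| 50% | 19% | 0.145 | 2.53 | 67% |

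Example, last row: 0.10 × 0.5 + 0.19 × 0.5 = 0.145, and 0.4286 / (0.145/0.855) = 2.53.

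This model keeps originating practices that give access at 10% while giving willing substitutes more, which is hard to justify if both are willing. A second model avoids that.

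**4. Effect of substitution: same true odds ratio in every practice**

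Assume a true odds ratio of 3.85 everywhere. Practices without access have control exposure pL, willing ones have pH, and all substitute controls come from willing practices. Case exposure within a practice is 3.85·o/(1 + 3.85·o), where o = p/(1 − p).

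| Share substituted | pL | pH | Odds ratio, own-practice controls | Odds ratio with the fallback |
|---|---|---|---|---|
| 10% | 8% | 10% | 3.85 | 3.76 |
| 25% | 5% | 10% | 3.80 | 3.28 |
| 50% | 5% | 10% | 3.77 | 2.75 |

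Example, second row: case exposure is 0.168 at pL and 0.300 at pH. The mix is 0.25 × 0.168 + 0.75 × 0.300 = 0.267, and (0.267/0.733) / (0.10/0.90) = 3.28.

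A Mantel-Haenszel estimate stratified by source type (originating or substitute) gives the same values as the last column, so stratifying on source does not remove the bias.

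**5. An opposing selection**

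The Discussion also asks whether specialists interested in bisphosphonates join more readily. If that raised case exposure, the two effects could cancel: 35% against 12% gives 3.95, and 40% against 15% gives 3.78. These figures too are assumed.

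**The case against.** - **The refusal mechanism is only a conjecture.** This stands. The Discussion says that dentists may lack motivation, and the condition is little experience of bisphosphonates or of delayed healing. It gives no refusal rate and no difference in use between practices. An originating practice has had at least one patient who became a case, so the description fits it less well, although that patient need not have used a bisphosphonate. The fallback is also triggered by any failure of access, not only by refusal.
- **The net direction is open.** This stands. A reader might infer that control exposure will be pushed up, that the association will be understated and that 90% power will not be reached. The protocol does not support that: its Discussion also raises case-side selection, which could push the odds ratio up, and says it is difficult to tell whether users are more or less likely to take part.
- **The fallback can be read together with the general rule on referring practices.** This is possible, and since all such specialists in Victoria are invited, a nearby practice's patients might well reach a participating one. But invitation is not participation, and staff following the fallback as worded would meet its conditions with a practice that refers to no participating specialist.
- **Analysis detail belongs in an analysis plan, and non-participation is already disclosed.** This is partly right. The absence of a sensitivity analysis from a condensed article is not itself a fault. Who may serve as a control is, however, a stated recruitment rule, and a later plan cannot separate the substituted sets unless their source was recorded. The disclosed limitation is not tied to the fallback.

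**Conclusion.** The point holds in a conditional form. The firm part is that the fallback omits the referral condition set elsewhere in the protocol, so it can admit controls who could not have become cases. That follows from the text and rests on no assumed number.

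The bias from willingness is a possibility, not a demonstrated effect. If practices without access have lower bisphosphonate use than their substitutes, an odds ratio above 1 moves toward 1. The movement ranges from negligible (3.86 to about 3.77) to substantial (about 2.53) over the mixture scenarios shown. Those results depend on substitution shares and exposure levels that the protocol does not give, and case-side selection could offset them. Nothing here disturbs the sample size calculation.

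**What to change.** In the section on recruitment of control subjects:

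1. Require a substitute to be a practice that refers to the case's specialist or, at the least, to a participating specialist. Use the referring-practitioner data already on the collection form. Keep proximity as a preference, not the qualifying condition.
2. Log every failure to obtain access.
3. Flag each matched set at recruitment as originating or substitute practice.
4. Report the bisphosphonate odds ratio in originating-practice sets beside the all-sets estimate.

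The first change addresses eligibility. It does not remove selection by willingness, because any substitute is still a practice that agreed; the restricted estimate is what can reveal that.

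The cost is a wording change, one flag variable, one extra model run and the work of compiling a list of referring practices. The form may not capture the referrer for every patient a specialist saw, so that list may take some effort. Some substitutes will lie further away, and the restricted estimate will be less precise.

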### Data Collection Methods

Data collection will involve collecting information pertaining to demographics, delayed dental healing, bisphosphonate history and medical history. Data collection forms and telephone interviews for controls will be the same as that used for cases.

#### Part 1: Demographic information

Specialist information, patient details (name, date of birth, gender, address and telephone number), name of referring practitioner, referring practitioner contact details, date of presentation of oral problem and referral to specialist date will be collected initially. A list of all dates within the visit window period together with an outline of each visit will be recorded. The demographic data will be coded for each individual and the code used in all subsequent data collection in order to de-identify information as per ethical requirements.

#### Part two: Delayed dental healing information

Each patient file identified within the visit window period will be analysed and information relating to the presence of an oral diagnosis (diagnosis, site, precipitant, treatment, outcome, biopsy report, radiographic investigation), bisphosphonate history and medical history (co-morbidities and medications) will be recorded.

The diagnosis will consist of the presence of either oral ulceration ("break in mucosa but no bone visible") or bone necrosis defined as "bone on view". A number of key words will be used when reviewing patient histories as a number of descriptors can be used to describe delayed dental healing. These will include non-healing socket, pus, exudate, swelling, draining sinus, dry socket, bone sloughing, sore sockets, OAC, oroantral communication, healing not completed, fistula, OAF, oroantral fistula, exposed bone and infection.

Information regarding site of the lesion will be further subdivided into single versus multiple sites, quadrant involved, palatal, lingual, buccal or labial orientation and tooth area (one to eight). The main precipitants listed can include tooth extraction, implant insertion, removal of pathological lesion, denture use, spontaneous, no obvious precipitant or other. In each case the date of the precipitant will be recorded. If the precipitant is not recorded in the history this will be marked as such on the data collection form.

Outcome of the delayed dental healing will be recorded by including treatment modalities such as antibiotics, mouthwashes/irrigation, debridement or other, date of the last review together with wound status (healed completely, healed partially, no healing or not recorded) and progress of the wound at the last visit (worse, stable, improving or not recorded). Details regarding any biopsy or radiographic analysis will also recorded.

#### Part 3: Medical History

Detailed information relating to potential cancer history including type, date of diagnosis, remission status, radiotherapy to the jaw and chemotherapy will be recorded as this is a key exclusion criterion. Other co-morbidities will be recorded including lung disease, heart disease, kidney disease, organ transplant, diabetes, rheumatoid arthritis or other connective tissue conditions together with smoking, tobacco and alcohol intake as these may contribute to delayed dental healing.

#### Part 4: Medication history

A detailed description of oral glucocorticoids (start/stop dates, current dose and cumulative dose), hormone replacement therapy and other medications including raloxifene, calcitriol, tibolone, teriparatide and strontium will be recorded.

If a bisphosphonate has been prescribed, the type will be recorded including alendronate, risedronate, tiludronate, pamidronate, zoledronate or etidronate together with indication for use (osteoporosis, Paget's disease, glucorticoid-induced osteoporosis, metastatic disease, hypercalcemia). Doses of all bisphosphonates including start and stop dates and current doses will be recorded to allow calculation of cumulative drug doses.

#### Telephone interview

A telephone interview will be conducted with all consenting participants in order to confirm inclusion/exclusion criteria (most of which may already be evident from the patient's dental file) and to determine socio-economic status, dental health information and a medical history check including bisphosphonate history, medication profile and smoking history. The telephone interview will last approximately 10 minutes. The telephone questionnaire will be modelled on the Adult Oral Health Survey [38] and include questions relating to dental health and general information such as socio-economic status and educational status. A medication check list will also be completed with each case regardless of the data collected in the original data collection form in order to cross match bisphosphonate history, other medical history which could contribute to impaired wound healing and smoking history.

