### Case Recruitment

Recruitment of individuals for the study is a two-step process, ascertainment of potential cases through dental record review then verification by a case adjudication panel (CAP). The research team would visit each participating practice to identify potential cases from the dental records, which could then in turn be presented to the case adjudication panel. Each specialist practitioner would be required to give consent to have patients in their practice contacted by the research team.

Participant ascertainment will occur through consecutive screening of oral and maxillofacial and special needs dental specialist records in private practices and public hospitals by trained research staff. Once a case has been confirmed by CAP, each specialist practitioner would be required to give consent to have patients in their practice contacted by the research team.

To be eligible for participation, the dental record should indicate that the potential participant is:

• age ≥ 50 years

• has a dental wound that failed to heal within 6 weeks

• had a qualifying visit during the window period.

The exclusion criteria are:

• A history of active malignancy or malignancy within five years (excluding basal or squamous cell carcinoma).

• Previous radiotherapy field that included the jaws.

• Bisphosphonate use for any indication other than post-menopausal osteoporosis or other benign bone disease.

In order for potential cases to be identified from the patient files, the research team reviewing the clinical notes need to be able to identify delayed dental healing. It is expected that the term "delayed dental healing" as a potential descriptor is unlikely to appear in the clinical notes, as there would be variability in clinical descriptions amongst specialists. As such a number of file terminology descriptors will be used to help identify potential cases of DDH and these are outlined within 'data collection methods' below.

All records identified as potential cases of delayed dental healing will be presented to the CAP for verification for inclusion or exclusion. The CAP will include a Chair who will be an independent specialist endocrinologist, 2 other medical practitioners and three dentists (one Oral Medicine Specialist, one oral and maxillofacial surgeon and one forensic dentist/bone biologist). A quorum of 4 (2 dental and 2 medical) will be required at each CAP meeting.

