At each CAP meeting all de-identified potential cases will be presented without the panel's knowledge of bisphosphonate history and medical status. The records presented will be assessed according to the previously stated inclusion and exclusion criteria.

Once verified as a definite case by the CAP, the individual will be contacted via mail to seek informed written consent for participation in the study. Non-responders will consist of two main groups; individuals who do not wish to participate and those who cannot be contacted (e.g. changed address or deceased).

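### One telephone call both confirms eligibility, which separates cases from controls, and takes the bisphosphonate history, with no masking of the caller described

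*Protocol article*

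**What the plan says.** All places are in the protocol article.

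- **Telephone interview.** A call of about 10 minutes is made to all consenting participants "in order to confirm inclusion/exclusion criteria (most of which may already be evident from the patient's dental file"). The same call covers "a medical history check including bisphosphonate history, medication profile and smoking history". The section adds a medication check list, used to cross-match the bisphosphonate history, and describes it as completed with each case. It does not mention controls.
- **Case Recruitment.** An eligible case "has a dental wound that failed to heal within 6 weeks". On finding cases: "The research team would visit each participating practice to identify potential cases from the dental records". On order: "Once verified as a definite case by the CAP, the individual will be contacted via mail to seek informed written consent". On masking: "all de-identified potential cases will be presented without the panel's knowledge of bisphosphonate history and medical status".
- **Recruitment of Control Subjects.** Controls "will have no known defect in dental wound healing".
- **Data Collection Methods.** "Data collection forms and telephone interviews for controls will be the same as that used for cases".
- **Discussion.** Participant recall is named as a limitation of the interview, and researcher interpretation as a limitation of the written records. An interviewer who knows the group is not mentioned.

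**The concern.** A case-control study compares exposure between people chosen by outcome, so the measurement most in need of protection from knowledge of the outcome is the exposure history. Here the masking runs the other way: the panel that classifies the outcome is kept from exposure. That is sound for case classification, but it does nothing for the person asking about bisphosphonates.

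A caller who knows that the participant has an unhealed jaw wound, and who knows the hypothesis, may probe harder for a drug and for its start and stop dates. The dates matter because the hypothesis concerns use for more than one year. Fuller elicitation in cases than in controls raises the odds ratio in the hypothesised direction. The planned logistic model cannot adjust for it, since the error lies in the exposure variable itself.

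**Working it through.** **1. Does the text expose case status to the caller?** Set side by side:

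| Step | What the text fixes | Consequence |
|---|---|---|
| Panel verification | Comes before contact by mail | Case status is settled before any call |
| Purpose of the call | Confirm inclusion and exclusion criteria | For cases these include the unhealed wound; for controls, no known healing defect |
| Same call | Bisphosphonate, medication and smoking history | Exposure is measured in the contact that confirms group-defining criteria |
| Check list | Described as completed with each case | Read literally, the caller must know who is a case to apply it |
| Masking | Panel only, to exposure and medical status | None described for exposure collection |

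No sentence says that callers are unmasked. The conclusion follows from the stated purposes of the call.

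**2. The plan's own figures.** With 30% use in cases and 10% in controls, OR = (0.30/0.70)/(0.10/0.90) = 3.86, against the stated value of around 3.85. Assuming a two-sided 5% test (the level is not stated) with continuity correction, 90% power needs 54 + 216 = 270, against the stated 54 + 215 = 269. The figures reproduce, and this point does not change them.

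**3. Illustration of size.** From the document: 10% use; 54 cases and 215 controls. Assumed: no true effect, no false reports of use, 95% of true use elicited in cases and a fraction *s* in controls. Recorded use is then 0.10 × 0.95 = 0.095 in cases and 0.10 × *s* in controls, and

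OR = [0.095/0.905] / [0.10*s*/(1 − 0.10*s*)].

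- *s* = 0.85: 0.10497/0.09290 = 1.13
- *s* = 0.80: 0.10497/0.08696 = 1.21
- *s* = 0.70: 0.10497/0.07527 = 1.39

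The rejection probability of a two-sided 5% test is found by summing the binomial probabilities of all 54-versus-215 tables that the test rejects:

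| Test | *s* = 0.95 (equal) | *s* = 0.80 | *s* = 0.70 |
|---|---|---|---|
| Pearson, uncorrected | 4.8% | 7.7% | 11.8% |
| Wald on log odds ratio | 3.2% | 6.3% | 10.2% |
| Fisher exact | 3.4% | 5.6% | 8.7% |
| Continuity-corrected | 2.5% | 4.6% | 7.4% |

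So rejection is about 5–8% at 80% elicitation in controls and 7–12% at 70%, depending on the test. Every test rises above its own equal-elicitation rate, although the conservative ones stay near or below 5% at 80%.

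**The case against.** The strongest reply is that much of this is inferred. The article does not say who makes the calls, what they are given or in what order items are asked, and a condensed article may leave such details to the full protocol. The interview section lists purposes, not a sequence. The wound criterion is documented in the dental record and verified by the panel before contact, so the call may in practice settle only malignancy, jaw radiotherapy and bisphosphonate indication, which need not reveal the group. Exposure is also recorded from the file, and forms and interviews are stated to be the same for both groups. The elicitation rates above have no source in the document.

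Much of that stands. A reader might infer that callers certainly know the group from the outset, that the file screeners make the calls, or that eligibility is asked before exposure. The text supports none of these as fact. Nor does it establish that controls are denied the check list: its wording is at odds with the statement that interviews are the same, and the two need reconciling. One eligibility item, the indication for bisphosphonate use, is itself an exposure question, so eligibility cannot all be moved to the end.

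What does not stand is that this is mere silence. The text assigns confirmation of inclusion as well as exclusion criteria to the call that measures exposure, and words the check list by case status. Identical forms do not stop a caller who knows the group from probing differently. The file data are only a partial safeguard: the Discussion concedes that records may be incomplete, and the file reviewer records the oral diagnosis alongside bisphosphonate history.

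**Conclusion.** The point holds as a cheap improvement, not as a flaw that undermines the study. As written, the caller can learn or must know case status when taking the exposure history, and the masking described does not cover that step. The likely direction is towards the hypothesis.

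The size cannot be derived from the document. Under the assumed elicitation rates the spurious odds ratio is 1.13 to 1.39, and the false-positive rate is modestly raised. Exposure already captured from files would shrink this further. A reader might infer that interviewer bias could by itself produce the planned odds ratio of 3.85; over the range examined it comes nowhere near.

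**What to change.** - Use one fixed script for cases and controls. Ask and close the medication and bisphosphonate items first (type, indication, start and stop dates, including the exclusion based on indication). Confirm wound-related eligibility last.
- Give callers an identifier and telephone number, without group or file data.
- Where possible, assign each call to an existing team member who did not screen that practice.
- State that the medication check list applies to controls as well as cases.
- Cross-match interview answers with the file afterwards, at data entry.

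The cost is reordering a 10-minute script and allocating calls within the present team; the sample size is unaffected. The downsides are that masking will fail when a participant mentions the wound, and that a few ineligible people will complete the medication section.
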